#### Secondary outcome analysis

ARM and EMG parameters, EORTC QLQ-CR29 scores: Analyzed using the same statistical methods as the primary outcomes.Statistical tests: continuous data: analyzed using Student’s *t*-tests, Mann-Whitney *U* tests, paired *t*-tests, and Wilcoxon signed-rank tests as appropriate. Categorical data: analyzed using chi-square tests or Fisher’s exact tests as appropriate.Reporting and significance: all *p*-values reported will be two-tailed. Confidence intervals will be set at the 95% level. Statistical significance will be defined as *p*-values < 0.05.

#### Additional notes

Detailed results and any supplementary analyses will be made available upon request.

By adhering to this structured SAP, we aim to provide clear, reliable, and interpretable results for both the primary and secondary outcomes of this study.

### Interim analyses {21b}

This trial is not subject to interim analyses.

### Methods for additional analyses (e.g., subgroup analyses) {20b}

Subgroup analysis will be performed for the radiotherapy group. Participants who have undergone pelvic radiotherapy related to rectal cancer will be included in the radiotherapy group.

### Methods in analysis to handle protocol non-adherence and any statistical methods to handle missing data {20c}

In cases where the lost-to-follow-up rates are below 20%, we will conduct an intention-to-treat analysis. Missing values will be replaced using single imputation procedures with the group mean.

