## Methods: participants, interventions, and outcomes

### Study setting {9}

Patients will be recruited from two tertiary hospitals: Sir Run Run Shaw Hospital (SRRH), affiliated with the Zhejiang University School of Medicine, and the First Affiliated Hospital of Zhejiang Chinese Medical University. Biofeedback sessions will take place at SRRH, while Percutaneous Electrical Pudendal Nerve Stimulation will be administered at the First Affiliated Hospital of Zhejiang Chinese Medical University. Evaluations will be conducted at both institutions.

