### Sample size {14}

Based on a prior study [10] involving 45 patients in each group (efficacy rate, 65.6%:46.7%), the required sample size for this study was computed utilizing the Power Analysis and Sample Size 15 software (NCSS Statistical Software, UT, USA). A sample size of 210 patients was determined to achieve a power (1-beta) of 0.80 and an alpha (significance level) of 0.05, with group allocation in a 1:1 ratio. Factoring in potential dropouts (15% of the participants), the total sample size was adjusted to 242 in total (*n* = 121 in each group).

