#### Data processing and preliminary steps

Normality test: Data will be assessed for normality using the Shapiro-Wilk test.Handling baseline imbalances: If baseline characteristics and outcome measures show imbalances, analysis of covariance (ANCOVA) will be applied to adjust for these differences.Data presentation: Normally distributed continuous variables will be presented as means ± standard deviations (SD). Non-normally distributed or ordinal variables will be presented as medians with interquartile ranges (IQR). Categorical variables will be presented as counts and proportions.Missing data: The last observation carried forward (LOCF) method will be used to handle missing data points. Other rules are referenced in Item 20c.

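### Intention-to-treat analysis is promised only while loss to follow-up is below 20%, so the analysis population depends on a post-randomisation result

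*Protocol article*

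**What the plan says.** Item 20c of the protocol article (non-adherence and missing data) has two sentences that matter here. The first sets the population: "In cases where the lost-to-follow-up rates are below 20%, we will conduct an intention-to-treat analysis". The second sets the imputation: "Missing values will be replaced using single imputation procedures with the group mean".

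The statistical analysis section, under data processing, gives a different imputation rule, "The last observation carried forward (LOCF) method will be used to handle missing data points", and refers to item 20c for other rules.

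The sample size section plans for loss: "Factoring in potential dropouts (15% of the participants), the total sample size was adjusted to 242 in total", that is, 121 per arm.

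On treatment burden, the study setting section puts the two treatments at different hospitals: "Biofeedback sessions will take place at SRRH, while Percutaneous Electrical Pudendal Nerve Stimulation will be administered at the First Affiliated Hospital". The intervention description gives both arms a 30-minute biofeedback session each weekday for 4 weeks. The intervention arm also has a 60-minute needling session on the same days.

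**The concern.** In a superiority trial, analysing everyone as randomised is what keeps the two groups comparable. That commitment should not depend on how the trial turns out. Here it lapses once loss reaches a set level, and loss is observed after randomisation and may be affected by treatment. If a population is chosen only after that point, nobody can later show that the choice was independent of the results.

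The trigger is also loosely defined. The article does not say whether 20% is an overall or a per-arm rate, or whether it applies at 1 month or 6 months. It does not say whether a patient whose treatment is stopped counts as lost.

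The extra daily session at a second hospital makes unequal attrition plausible. The document gives no figure for it.

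**Working it through.** **Inputs.** 242 randomised, 121 per arm, 15% planned loss, efficacy rates 65.6% and 46.7%, power 0.80, alpha 0.05 (sample size section); two-sided tests (secondary outcome analysis section); 20% limit (item 20c). True loss rates other than 15% are assumptions.

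**1. The plan's own figure.** Two proportions, unpooled normal approximation:

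n per arm = (1.960 + 0.842)² × [0.656 × 0.344 + 0.467 × 0.533] / (0.656 − 0.467)² = 104.3, rounded up to 105, so 210 in total. This matches. Then 210 × 1.15 = 241.5, which gives the stated 242. So 242 patients with 15% expected loss is the right baseline for checking the trigger.

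**2. Where the trigger lies.** Overall: 0.20 × 242 = 48.4, so 49 or more lost. Per arm: 0.20 × 121 = 24.2, so 25 or more lost in that arm.

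**3. How likely it is.** Losses are treated as independent with a common true rate q.
- Overall reading: P(X ≥ 49), X ~ Binomial(242, q).
- Either-arm reading: 1 − [1 − P(Y ≥ 25)]², Y ~ Binomial(121, q).

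| True loss q | Overall ≥ 20% | Either arm ≥ 20% |
|---|---|---|
| 15% (planned) | 1.7% | 11% |
| 18% (assumed) | 20% | 45% |
| 20% (assumed) | 49% | 71% |
| 22% (assumed) | 77% | 89% |

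At the planned rate the two readings differ more than sixfold, so the missing definition matters. For example, 30 patients lost from one arm and none from the other is 30/121 = 24.8% of that arm but 30/242 = 12.4% overall. Intention-to-treat lapses on one reading and holds on the other.

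**4. Would unconditional intention-to-treat be enough?** Suppose n patients are randomised to an arm, k of them are observed, and the observed mean is m. Filling the other n − k values with m gives an arm mean of [k·m + (n − k)·m]/n = m. The difference between arms is then exactly the completers' difference. An analysis labelled intention-to-treat but imputed this way carries the same attrition bias as a completers analysis, at any level of loss. (This takes the group to be the allocated arm.)

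It also makes the standard error too small, because the imputed values add to n but not to the variation. In simulation with normal data, 121 per arm and no true effect, a nominal 5% t-test rejected in about 8%, 9% and 12% of trials at 10%, 15% and 20% missing.

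**The case against.** Four points can be made on the other side.

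**The trigger is unlikely on the document's only figure.** This stands for the overall reading at 15% loss (1.7%). It does not justify the rule, which acts only when attrition is heavier than planned.

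**A fuller analysis plan may name what happens at 20% or more.** The article says a comprehensive plan exists, and it is not shown. The missing fallback is therefore not the finding. The stated condition is: a fuller plan would either repeat it or contradict it.

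**Stronger readings go beyond the text.** A reader might infer that randomisation is given up above 20%, or that a completers or per-protocol analysis takes over. The article says neither; it only stops promising intention-to-treat. A reader might also infer that the rule would favour the combined treatment, because patients who cannot manage needling would drop out as non-responders. That is not supported. Stopping treatment is not loss to follow-up: the article provides for telephone follow-up personnel and evaluations at both hospitals. Participants are not blinded, so disappointed controls could leave too. Nor does anything suggest that the count of losses would be manipulated; data collectors and statisticians are to be blinded.

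**The imputation rule, not the condition, carries most of the attrition bias.** This stands in large part. As step 4 shows, removing the condition while keeping group-mean imputation leaves the estimated mean difference equal to the completers' one. The two must be corrected together.

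**Conclusion.** The concern holds in a limited form. The article makes intention-to-treat conditional on loss below 20%, so from 49 losses in 242 (overall reading) analysis of all randomised patients as allocated is no longer guaranteed. This is a rule that is stated and badly set, not a detail left out.

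The chance of reaching the limit at the planned 15% loss is about 1.7% overall, or about 11% if either arm counts. It rises quickly if true loss is higher. These figures assume independent losses at the same rate in both arms; rates above 15% are illustrative.

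No size or direction of bias can be given from the document. The difference in treatment burden is a reason for caution about unequal loss, not evidence of it.

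**What to change.** Replace the conditional sentence in item 20c with, for example: the primary analysis includes all randomised patients in their allocated arm, whatever the loss to follow-up; per-protocol and completers analyses are supportive only. State that outcomes continue to be collected at 1 and 6 months after a patient stops treatment.

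In the same amendment, replace group-mean imputation with multiple imputation or a likelihood-based model. Reconcile this with the last-observation-carried-forward rule under data processing, so that one primary method remains. Add missing-not-at-random (tipping-point) sensitivity analyses. If a 20% level is kept, it should prompt extra sensitivity analyses rather than decide the population, and it should be defined as overall or per arm and by visit.

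The cost is one sentence for the population and a short paragraph for missing data, plus modest programming. The sample size is unaffected. The change should be dated and made before the allocation codes are broken.

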## Discussion

The management of LARS is crucial considering its high prevalence and severe impairment of the quality of life [26]. The treatment timing is important, and early intervention for LARS is preferred as it is better for neural functions [27]. Therefore, as per our protocol, our intervention can start 1 month postoperatively for anal preserve rectal cancer or temporary ileal stoma retraction.

Opting for a combined approach of biofeedback and PEPNS for treating LARS is grounded in their potential synergistic action in LARS management as well as their high operational feasibility. Biofeedback, utilizing superficial electrodes and anal internal sensing probes, accurately detects pelvic muscle movements, providing effective guidance to patients during pelvic floor exercises. It also promotes pelvic muscle rehabilitation through superficial electrical stimulation. On the other hand, PEPNS precisely locates the perineal nerve positions via percutaneous needling, directly stimulating these nerves to increase the resting sphincter pressure, thereby enhancing bowel control. Biofeedback is a routine outpatient procedure conducted in many tertiary hospitals, whereas PEPNS implementation only requires an acupuncture apparatus and basic training for physicians in needling techniques, which can be easily sought in Chinese medicine hospitals. Hence, the execution of this study is comparatively straightforward.

The symptoms of LARS tend to be more severe in the initial months after surgery, especially in the first 4 months, followed by a gradual improvement and stabilization between 6 months to 1 year [4, 5]. Therefore, our assessments not only include a short-term evaluation 1 month after treatment but also a long-term evaluation after 6 months. This is aimed at minimizing potential biases due to natural symptom variations over time. Additionally, based on the results from the 6-month long-term evaluation, we will determine the necessity for further assessment after 1 year.

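### Two single-imputation rules, last observation carried forward and group mean, cover the same missing value; read as the arm mean, the second raises the t-test's 5% error to about 9.6% at the planned 15% loss

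*Protocol article*

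**What the plan says.** The two rules stand in different sections of the protocol article.

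- Under Data processing and preliminary steps: "The last observation carried forward (LOCF) method will be used to handle missing data points. Other rules are referenced in Item 20c".
- Item 20c first sets a condition, "In cases where the lost-to-follow-up rates are below 20%, we will conduct an intention-to-treat analysis", and then gives its own rule: "Missing values will be replaced using single imputation procedures with the group mean".

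These sections determine what the rules act on:

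- **Outcome {12}:** assessments at baseline, 1 month and 6 months. The primary outcome is the percentage improvement in LARS score, and treatment counts as effective above 25%.
- **Primary outcome analysis:** arms are compared on improvement rates by an independent-samples t-test, or by a rank test if the data are not normal. The secondary outcome section sets two-tailed p-values and significance below 0.05.
- **Sample size {14}:** "Factoring in potential dropouts (15% of the participants), the total sample size was adjusted to 242 in total", that is 121 per arm.
- **Discussion:** symptoms are worst in the first months after surgery, "followed by a gradual improvement and stabilization between 6 months to 1 year".

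**The concern.** Neither rule is limited to a variable, a visit or a reason for missingness. The analyst can therefore choose between two values for the same missing observation, and the primary result can depend on that choice.

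Each rule also has its own fault. Replacing missing values with the arm's mean adds patients who have no spread and who repeat the observed arm difference, so the standard error is too small and the test rejects too often. Carrying the last score forward assumes nothing changes after the last visit, which is not what the Discussion describes. At stake are the p-value and confidence interval of the primary comparison.

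**Working it through.** **The plan's own figure.** Inputs from Sample size {14}: 65.6% v 46.7%, two-sided 0.05, power 0.80. With the unpooled formula, n per arm = (1.960 + 0.842)² × [0.656 × 0.344 + 0.467 × 0.533] / 0.189² = 104.3, so 105 per arm and 210 in total, as stated. Then 210 × 1.15 = 241.5, so 242. The 15% loss and 121 per arm are therefore the plan's own working values.

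**Overlap of the rules.** Take a patient with scores at baseline and month 1 and none at month 6. Carrying forward inserts that patient's month-1 score. The group-mean rule inserts the mean of the other patients' month-6 values. The two agree only by coincidence.

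**Arm-mean imputation and the t-test.** Let d be the fraction missing completely at random, and n the number per arm.

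- True variance of an arm mean: σ²/[n(1 − d)], because only the observed patients carry information.
- Variance the t-test uses: about σ²(1 − d)/n, because the filled-in values have no spread but are counted in n.
- Ratio of standard errors: (1 − d). Exactly, with 103 of 121 observed: √[(102/120) × (103/121)] = 0.851.
- Actual type I error: 2[1 − Φ(1.96(1 − d))].

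| Missing | Formula | Simulated (121 per arm, 20,000 runs) |
|---|---|---|
| 5% | 6.3% | 6.0% |
| 10% | 7.8% | 7.8% |
| 15% (planned) | 9.6% | 10.1% |
| 20% (Item 20c limit) | 11.7% | 11.5% |

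Coverage of the 95% interval at 15% missing is 100 − 9.6 = about 90%.

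**If the post-treatment score is imputed and the rate then derived.** With illustrative LARS means, standard deviations and correlations, the simulated error at 15% missing was about 8 to 10%. For a plain change score with equal variances and a correlation of 0.5, the ratio of standard errors is √(1 − d), which gives 2[1 − Φ(1.96 × √0.85)] = 7.1%.

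**If a mean over both arms was meant.** Simulated type I error stays at 4.9 to 5.2%. The expected arm difference is multiplied by (1 − d), which is 0.85 at 15% missing.

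**Response above 25%.** If the improvement rate itself is imputed, all missing patients in an arm are classed alike. A true rate p becomes (1 − d)p + d when the arm mean exceeds 25%, and (1 − d)p otherwise. At d = 0.15:

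- 46.7% becomes 54.7% or 39.7%.
- 65.6% becomes 70.8% or 55.8%.
- The 18.9-point difference becomes 0.85 × 18.9 = 16.1 points if both means lie on the same side of 25%. It becomes 16.1 + 15 = 31.1 points if the intervention mean lies above and the control mean below.

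If the score is imputed first, each patient's own baseline still affects the classification, so it is not all or nothing.

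**Carrying forward.** Let g be the mean improvement after the last observed visit among those lost. The bias in the arm difference is −(d₁g₁ − d₂g₂), where 1 is the intervention and 2 the control. It is zero with equal losses and equal gains, and otherwise can take either sign.

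**The case against.** **The cross-reference.** The sentence on carrying forward is followed by a pointer to Item 20c, so the two passages were meant to be read together. That is fair, but Item 20c supplies a second general rule and does not say which values it governs. The conflict stands. It is also not detail left to a fuller plan, since the article states both rules itself.

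**The meaning of group mean.** The inflation depends on reading it as the arm mean. This is the natural reading, because the article uses group for the arms throughout, but it is a reading.

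**The responder outcome.** A reader might infer that arm-mean imputation gives the responder comparison a type I error of 33% to 48%, or turns the planned 18.9 points into about 28. The documents do not support this. Those values arise only if the improvement rate itself is imputed, with an assumed standard deviation of 30. The error figures also need a common response rate near 50%, and the 28 points average over the two cases of 16.1 and 31.1. At common rates of 35 to 40% or 60 to 66% the error is back near 5%. If the post-treatment score is imputed first, it was 8 to 15% under assumed score distributions. The primary outcome analysis section also names no responder test.

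**Direction of error.** A reader might also infer that both rules favour a positive result. Only arm-mean imputation is anti-conservative. Carrying forward would work against the intervention if that arm lost more patients who were still improving. Any figure for that bias needs gains and losses by arm that the article does not give.

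**Conclusion.** The plan is wrong as written on two counts. First, it states two incompatible rules for the same missing value. This needs no assumption.

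Second, the rule in Item 20c makes the planned t-test anti-conservative: about 9.6% instead of 5% at the planned loss and 11.7% at the 20% limit. These figures assume the arm mean, data missing completely at random, and imputation of the analysed variable. Imputing the score first gives about 8 to 10% for the improvement rate at the planned loss. A doubling of the error therefore belongs to losses of about 15%; at 5 to 10% missing the inflation is smaller.

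The classification of response is also distorted, but its size depends on which variable is imputed and how close the arm mean lies to 25%, so no single figure should be attached to it. Carrying forward is not a safe replacement, given the course of symptoms in the Discussion, but the direction of its bias is unknown.

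**What to change.** Delete both single-imputation rules and state one rule for all randomised patients:

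1. Impute the missing LARS score by multiple imputation within arm, from baseline and earlier scores and other baseline covariates already collected, such as prior radiotherapy.
2. In each imputed data set, derive the percentage improvement and the response above 25% as the primary outcome section defines them. Analyse each data set and pool.
3. For the continuous analysis, a likelihood-based repeated-measures model is an acceptable alternative if it models the same outcome. A model of raw LARS scores would change the outcome from percentage improvement and would have to be declared as such.
4. Add a sensitivity analysis with missing counted as non-response. This is itself a single imputation, so it should not be the main analysis.

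Settle the wording before unblinding. The cost is somewhat more analysis work and wider confidence intervals, which reflect the information actually observed. Recruitment, visits and treatment are unaffected.

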### Plans to give access to the full protocol, participant-level data, and statistical code {31c}

The datasets analyzed during this trial can be made available from the corresponding author upon reasonable request.

### Composition of the data monitoring committee, its role, and reporting structure {21a}

The clinical trial will not incorporate an external data monitoring committee due to the utilization of therapies commonly practiced by pelvic physical therapists and acupuncturist and assessments frequently administered to rectal cancer patients. However, an internal committee will be established to monitor preliminary safety data. This committee will comprise the researchers responsible for assessing the primary outcomes and the principal investigator. They will conduct ongoing preliminary data analyses to assess safety and efficacy. In the event of any reported adverse events, this committee will seek analysis and recommendations from an external surgeon with expertise in treating rectal cancer. The data monitoring group operates independently from the funder and sponsor.

### Adverse event reporting and harms {22}

The study will monitor for PEPNS-related adverse events (AEs), such as needle-related infections, and report them to the Ethics Committee. We will document the site, extent, treatment process, and recovery time of each AE, and assess the causality between AEs and the intervention. AEs will be used as safety outcome measures to evaluate the safety of the intervention.

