
Therefore, the application of PEPNS along with biofeedback could be an effective and economical non-surgical treatment for LARS. This study aims to conduct a randomized controlled trial (RCT) to compare the efficacy and safety of this combined approach with biofeedback alone.

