#### Patients in this group will receive a combined treatment of biofeedback and PEPNS

Biofeedback Therapy: Patients will be positioned in a semi-supine stance at a 120° angle, maintaining relaxed arms and extended legs. Following lubrication, electrode probes will be carefully inserted into the anal canal and rectum, linking to a biofeedback stimulator. Patients will receive guidance to engage specific muscles—primarily the anal and pelvic floor muscles—while consciously avoiding the activation of the abdominal or thigh musculature. The therapy regimen will involve a dual-step process with initial training (Kegel template training) comprising controlled contractions for 10 s, followed by a 10-s rest period, guided by pelvic floor EMG data. Subsequent sessions will include electrical stimulation training, contingent upon preset thresholds correlated with pelvic muscle contractions. This 30-min therapy session will be conducted once daily from Monday to Friday over 4 weeks, with rest on the weekends.

PEPNS: Patients will be asked to assume a prone position. Four specific points along the caudal sacrum will be selected in alignment with the pudendal nerve direction. The puncture sites have been described in detail in the illustration in our previous study [22]. We will target the upper points (adjacent to the sacrococcygeal joint symmetrically on both sides) and lower points (located 1 cm from the coccyx tip on each side). Long acupuncture needles (0.4 mm × 100 mm; Suzhou Shenlong Medical Apparatus Factory, Suzhou, China) will be vertically inserted 75–90 mm deep at the upper points and diagonally toward the lateral side (in the direction of the ischiorectal fossa) at a depth of 90–95mm at the lower points. These needles will be connected to electrodes on a G6805 electro-acupuncture apparatus to deliver continuous electrical stimulation at a frequency of 2 Hz and intensity adjusted to each patient’s tolerance. Each PEPNS session, lasting 60 min, will be conducted Monday to Friday for 4 weeks, with rest on the weekends.

(2) Control group (biofeedback alone)

Patients in this group will exclusively undergo biofeedback treatment, following the same procedures detailed previously for the intervention group.

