### Criteria for discontinuing or modifying allocated interventions {11b}

If a needlestick infection occurs during PEPNS, the treatment will be delayed, and antibiotics will be administered. If symptoms improve within 1 week, treatment will continue. If symptoms do not improve within 1 week, or if another infection occurs after improvement, treatment will be terminated. Meanwhile, this should be reported as an adverse event. And if any other unforeseen serious side effects occur, the intervention will also be terminated.

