### Procedure for unblinding if needed {17b}

If a serious adverse event occurs, the participant’s allocation will be unblinded. The incident will be promptly reported to the Ethics Committee.

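### The stated scope of adverse event monitoring is PEPNS-related events, which control patients cannot have, so it does not support the between-arm safety comparison announced in the background

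*Protocol article*

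**What the plan says.** The last sentence of Background and rationale {6a} says that the trial will "compare the efficacy and safety of this combined approach with biofeedback alone".

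Adverse event reporting and harms {22} sets the scope of monitoring: "The study will monitor for PEPNS-related adverse events (AEs), such as needle-related infections, and report them to the Ethics Committee". It goes on to say that the details of each event will be documented, that the investigators will "assess the causality between AEs and the intervention", and that "AEs will be used as safety outcome measures to evaluate the safety of the intervention".

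Intervention description {11a} says of the control group: "Patients in this group will exclusively undergo biofeedback treatment, following the same procedures detailed previously for the intervention group". The biofeedback common to both arms is invasive: "electrode probes will be carefully inserted into the anal canal and rectum, linking to a biofeedback stimulator".

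Three other sections mention harms without limiting them to PEPNS:
- Procedure for unblinding {17b}: "If a serious adverse event occurs, the participant’s allocation will be unblinded", with a report to the Ethics Committee.
- Criteria for discontinuing or modifying interventions {11b}: "if any other unforeseen serious side effects occur, the intervention will also be terminated".
- Data monitoring committee {21a}: an internal committee watches preliminary safety data and seeks an external surgeon's advice on any adverse event that is reported.

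**The concern.** A comparison of safety needs events that are looked for in the same way in both arms. Here the monitored category is defined by a treatment that only one arm receives. A control patient with perianal pain or bleeding after a probe session does not fall under it. An intervention patient with the same symptom falls under it only if somebody links the symptom to the needles.

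Two errors become possible, in opposite directions. A background event in the intervention arm may be blamed on PEPNS, with no control rate to set against it. A real excess that nobody recognises as PEPNS-related may go unrecorded. Participants and operators know the allocation (Discussion; Who will be blinded {17a}), so attribution could be influenced by that knowledge, although the harms section does not say who judges relatedness. An analysis plan cannot repair this later, because it cannot recover events that were never recorded.

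**Working it through.** The document gives no figure on safety, so there is nothing to reproduce. The check sets the sections side by side.

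1. **What is to be compared.** The combination against biofeedback alone, on safety (closing sentence of {6a}). This needs a count in each arm.
2. **What is routinely monitored.** PEPNS-related events ({22}), with needle-related infection as the only example. No other section states a scope for routine monitoring.
3. **Who can have such an event.** Only patients given PEPNS. Controls have biofeedback exclusively ({11a}), so their count in this category is 0 of 121 whatever harms they suffer (121 per group from Sample size {14}). This zero applies to the PEPNS-related category and to nothing wider.
4. **What is left without a stated route.** Non-serious harms of the anal-probe biofeedback in either arm, and non-serious harms in the intervention arm that are not recognised as PEPNS-related.
5. **Whether other sections fill the gap.** {17b} is an unblinding and reporting rule for serious events. {11b} is a stopping rule. {21a} is an escalation rule that starts once an event has been reported. All three can apply to a control patient, but none says that both arms are asked the same questions at the same times.
6. **Whether the harms section is consistent with itself.** It assesses causality on the documented events. If those events are already limited to PEPNS-related ones, this step has little left to decide. If the step is meant in earnest, the opening sentence describes the scope too narrowly. Either way, the wording needs reconciling.

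**Direction of the possible error (illustration only).** Let b be the rate of local symptoms not caused by PEPNS, equal in both arms, and a the share of those in the intervention arm that is attributed to PEPNS. Then:

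reported difference in the monitored category = a × b − 0, while the true difference is 0.

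As a runs from 0 to 1, the reported difference runs from 0 to b:

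| Assumed b | Expected patients per arm (121 × b) | Reported difference |
|---|---|---|
| 2% | 2.4 | 0 to 2 points |
| 5% | 6.1 | 0 to 5 points |
| 10% | 12.1 | 0 to 10 points |

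Conversely, suppose that PEPNS raised a non-serious symptom from 10% to 20% and none of it was attributed to PEPNS. The true difference would be 10 points and the reported difference 0. Every rate here is an assumption, and the table does no more than restate it. It shows that the result would depend on attribution, not how large the bias will be.

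**The case against.** The best case for the plan has five parts.

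- **The harms section does not say that other events are ignored.** This is true. Exclusivity is an inference from a sentence that names one category. Yet no other section provides for routine collection in controls, and if wider collection is intended the sentence needs correcting anyway.
- **Causality is assessed on documented events, which is the right order.** This also stands as far as it goes. A reader might infer that attribution is used throughout as a filter before counting. The text does not establish that. It leaves the two sentences of the section at odds.
- **Control patients are not outside all safety oversight.** A reader might infer that the control arm can have no adverse events by construction. The documents do not support this, because a serious event in a control patient leads to unblinding and a report to the Ethics Committee, and the internal committee acts on any reported event. The fixed zero holds only for PEPNS-related events.
- **The comparative aim is thinly anchored.** It stands in the background. Objectives {7} names symptoms and quality of life, the list of secondary outcomes contains no adverse events, and the harms section speaks only of the safety of the intervention. This makes narrowing the background sentence a legitimate alternative. It also means that no false-positive rate for a between-arm test can be held against the plan, since no such test of adverse events is specified.
- **Detail is normally left to the full protocol.** Question wording, visit forms and summary measures are indeed not missing from an article. The point here is not silence: a stated scope conflicts with a stated aim.

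**Conclusion.** The point holds in a limited form. The monitoring scope stated in {22} and the exposure stated in {11a} together cannot deliver the safety comparison stated in {6a}, and the rules in {11b}, {17b} and {21a} do not provide equal ascertainment. It would go too far to say that nothing about comparative safety could be learned, because serious events can come to light in either arm.

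The conclusion rests on reading the opening sentence of {22} as the scope of routine monitoring, which is the natural reading but not an explicit restriction. The size of the bias cannot be derived from the documents, and any background rate is an assumption. The efficacy result is untouched. The change should be made because a stated aim cannot be met as written and missed events cannot be recovered later.

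**What to change.** Change {22} so that all adverse events, whatever their cause, are recorded in both arms, with the same questions, at contacts that already exist: the weekly talks in {11c} and the 1- and 6-month assessments in {12}. Assess relatedness to PEPNS and to biofeedback afterwards, as an attribute of each recorded event. Report by arm the number and proportion of patients with any adverse event and with any serious adverse event.

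The collection must respect {17a}, where data collectors and telephone follow-up staff are blinded and operators take no part in data recording. Questions about needle sites would reveal the arm, so these items should be kept away from the blinded outcome assessors, for example on a separate patient-completed form. Participants know their allocation, so this protects the assessors' blinding but does not make reporting itself blind.

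If the sponsor does not want this, narrow the closing sentence of {6a} to a description of PEPNS-related harms in the intervention arm and make no comparative safety claim.

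Cost: a few more records and one separate form. Treatment, visits and sample size do not change. For patients already treated, events not recorded at the time cannot be fully recovered, so the report should state the date from which the common form was used.
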